#### Participants withdrawal

The patient has the right to voluntarily discontinue participation in the trial for any reason at any time, and the investigator also has the right to discontinue the patient’s participation in the trial at any time.

Reasons for discontinuing participation in a clinical trial may include, but are not limited to:
Withdrawal of consent from patientsTermination of testing or closing of testing institutionsNon-compliance of patients defined as non-compliance with the clinical trial plan requirements according to the decisions of the tester or clientOccurrence of serious adverse events

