### Criteria for discontinuing or modifying allocated interventions {11b}

Suspension of administration: If the following serious adverse reaction occurs during the administration of the test drug, administration shall be stopped immediately.
Symptoms of shock or anaphylaxisSevere hyperkalemia: when there is a change in the electrocardiogram due to hyperkalemia or when the potassium blood concentration is above 7.0 mEq/LSevere hyponatremia: sodium blood concentrations below 120 mEq/L

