### Plans to promote participant retention and complete follow-up {18b}

#### Participants retention

Once a participant is enrolled or randomized, the researcher will make every reasonable effort to follow the participants for the entire study period. The research nurse will contact the participants before the scheduled follow-up date to avoid loss of follow-up.

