## Statistical methods

### Statistical methods for primary and secondary outcomes {20a}

Intention-to-treat analysis and per protocol analysis will be conducted respectively, and intention-to-treat analysis will be performed as the main analysis.The categorical variable of the evaluation index will be analyzed using Pearson’s chi-square test, and the continuous variable will be analyzed using ANOVA or Kruskal–Wallis test.The virus removal rate on day 14, one of the secondary outcomes, will be analyzed using Pearson’s chi-square test.Time to clinical improvement will be assessed on all subjects by day 28. If there is no clinical improvement or a case of death by day 28, it will be recorded as day 28, and analyzed by Kaplan–Meier plot and log-rank test.

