## Methods in analysis to handle protocol non-adherence and any statistical methods to handle missing data {20c}

Outcome data obtained from all randomized participants will be included in the main analyses to prevent attrition bias. To prevent missing data, the researcher, trained research nurse, and research assist will double check the data as well as the recording of reasons for missing data. By replacing missing data with the mean or median value, we plan to analyze with minimal data loss.

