### Adverse event reporting and harms {22}

In our study, an adverse event will be defined as medical occurrence in a subject with regard to the possibility of a causal relationship. Adverse events will be collected after the subject has provided consent and enrolled in the study. If a subject experiences an adverse event after the informed consent document is signed (entry) but the subject has not started to receive study intervention, the event will be reported as not related to study drug. All adverse events occurring after entry into the study and until hospital discharge will be recorded. An adverse event that meets the criteria for a serious adverse event (SAE) between study enrollment and hospital discharge will be reported to the Gyeongsang National University Hospital IRB [Institutional Review Board] as an SAE. A serious adverse event for this study is any untoward medical occurrence that is believed by the investigators to be causally related to study drug and results in any of the following: life-threatening condition (that is, immediate risk of death), severe or permanent disability, prolonged hospitalization, or a significant hazard as determined by the Data Safety Monitoring team. Serious adverse events occurring after a subject is discontinued from the study will not be reported unless the investigators feels that the event may have been caused by the study drug or a protocol procedure. Investigators will determine relatedness of an event to study drug based on a temporal relationship to the study drug, as well as whether the event is unexpected or unexplained given the subject’s clinical course, previous medical conditions, and concomitant medications.

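### The withdrawal rule lets investigators end trial participation, not only treatment, for a serious adverse event or non-compliance, which puts the intention-to-treat analysis at risk

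*Protocol article*

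**What the plan says.** All references are to the protocol article.

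- **Participants withdrawal, in {18b}.** Besides the patient's own right to leave, "the investigator also has the right to discontinue the patient’s participation in the trial at any time". The reasons are open-ended ("Reasons for discontinuing participation in a clinical trial may include, but are not limited to") and include withdrawn consent, closure of the trial or a site, non-compliance as judged by the study side, and serious adverse events. What ends is participation in the trial.
- **Discontinuing or modifying interventions, {11b}.** Stopping the drug has its own rule: "If the following serious adverse reaction occurs during the administration of the test drug, administration shall be stopped immediately". The withdrawal text does not refer to it.
- **Participants retention, in {18b}.** After enrolment or randomization, "the researcher will make every reasonable effort to follow the participants for the entire study period".
- **Statistical methods, {20a}.** "intention-to-treat analysis will be performed as the main analysis".
- **Non-adherence and missing data, {20c}.** "Outcome data obtained from all randomized participants will be included in the main analyses to prevent attrition bias", and "By replacing missing data with the mean or median value, we plan to analyze with minimal data loss".
- **Adverse event reporting, {22}.** "Serious adverse events occurring after a subject is discontinued from the study will not be reported unless the investigators feels" that the drug or a protocol procedure may have caused the event. The same section counts an event as serious only if the investigators believe the study drug caused it.

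**The concern.** An intention-to-treat analysis needs the outcome of every randomized patient, including those who stop the drug or depart from the protocol. The withdrawal text treats two events that occur after randomization as grounds for leaving the trial altogether. A site could reasonably read it as permission to stop assessing such a patient.

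Two features make this more than loose wording. First, the trial is open label, so whoever decides on removal knows the allocation, and under {18a} the clinician also rates the ordinal scale. Second, controls receive no study drug, so an event defined as caused by that drug can in effect arise only in the nafamostat arm. Loss for this reason would therefore depend on the arm. If it also tends to involve patients who have not improved, the comparison shifts in favour of nafamostat. Outcomes that sites were allowed not to collect may not be recoverable by any later analysis.

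**Working it through.** **Step 1. Set the passages side by side.**

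| Question | Text that allows loss | Text that opposes it |
|---|---|---|
| What may end? | Trial participation ({18b}, withdrawal) | Only the infusion ({11b}) |
| Who is followed? | Not stated after discontinuation; routine serious-event reporting ends ({22}) | Everyone, within reasonable effort ({18b}, retention) |
| Who is analysed? | Missing values are replaced ({20c}) | All randomized participants ({20a}, {20c}) |

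Because {11b} already covers stopping the drug, the withdrawal text cannot be read as merely a drug-stopping rule. Nothing in the article says what is collected once participation has ended for one of the listed reasons.

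**Step 2. Does the missing-data rule repair the loss?** The primary outcome is binary (improved or not), with planned rates of 80% and 90% under Sample size {14}. When more than half of patients improve, the median of a 0/1 outcome is 1, so median replacement records a removed non-improver as improved. The mean is a fraction, which cannot be placed in a cell of the Pearson chi-square table planned in {20a}. Neither choice restores the true value.

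**Step 3. Illustrate the size.** The point depends on no figure in the plan, so there is none to reproduce.

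Inputs:
- From {14}: 42 patients per arm (taken as stated), 80% control rate, 10-point planned difference, 5-point margin and 5% dropout per arm.
- Assumed: nafamostat has no effect, so x = 34 of 42 improve (0.80 × 42 = 33.6, rounded to 34; 34/42 = 81.0%).
- Assumed, as a worst case: k patients are removed, all of them non-improvers in the nafamostat arm, and none is removed from control.
- k = 2 is about the planned dropout (0.05 × 42 = 2.1). k = 4 is 4/42 = 9.5%, about twice that.

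Formulas: removed patients dropped, x/(n − k); median replacement, (x + k)/n.

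| k | Dropped | Shift | Median replacement | Shift |
|---|---|---|---|---|
| 0 | 34/42 = 81.0% | 0 | 34/42 = 81.0% | 0 |
| 2 | 34/40 = 85.0% | 4.0 points | 36/42 = 85.7% | 4.8 points |
| 4 | 34/38 = 89.5% | 8.5 points | 38/42 = 90.5% | 9.5 points |

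The median column is the closer match to the plan, since {20c} replaces missing values rather than dropping patients. If outcomes are collected on everyone, the rate stays at 81.0%.

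**Step 4. Effect on the false-positive rate, under the same worst case.** Take a true rate of 80% in both arms and let a fraction f of the nafamostat arm, all non-improvers, be dropped. The observed rate is then p = 0.80/(1 − f). For a one-sided 0.05 test of no difference (normal approximation, no margin), the false-positive rate is

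1 − Φ(1.645 − (p − 0.80)/√[p(1 − p)/(42(1 − f)) + 0.16/42]).

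- f = 0.05: p = 84.2%, rate about 13%.
- f = 0.10: p = 88.9%, rate about 30%.

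Both compare with a nominal 5%.

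**The case against.** The strongest reply is that the withdrawal text only permits removal and that nothing in the article says outcome collection then stops. The retention text in the same section commits to follow-up, {20c} includes all randomized participants, {30} plans contact after discharge and {18a} collects reactions to day 28. The article also condenses a fuller protocol, which may say what happens after discontinuation.

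Much of this stands, and it limits the point. A reader might infer that the patients who do worst will lose their day-14 and day-28 outcomes and that the intention-to-treat analysis cannot be carried out. The documents do not support that:

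- Loss is possible under the rule, not prescribed by it. An analysis of all randomized patients could still be run with replaced values, though it could be biased.
- A drug-attributed event, or non-compliance, is not the same as the worst clinical course. That removed patients would be non-improvers is an assumption.
- The sentence in {22} concerns serious-event reporting, not the ordinal scale or vital status. Its exception for events possibly caused by the drug or a procedure covers essentially all events that meet the article's own definition, so it does not show that later serious events would be hidden.
- Non-compliance is defined against the trial plan, which binds both arms, and treatment is given in hospital ({11c}). The arm-dependence argument rests on the serious-event reason.
- At about the planned dropout the worst-case shift is 4.0 to 4.8 points, below the 5-point margin. The larger shifts need about twice that loss.

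What remains is that the stated rule ends participation for reasons that arise after randomization, and that it sits against the retention and analysis statements. A fuller document could resolve this, but the text as published points sites in two directions.

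**Conclusion.** The point holds as a conflict within the protocol and a risk to the main analysis. The withdrawal rule permits loss of follow-up that may be related to outcome and, through the drug-related definition of a serious adverse event in an open-label trial, to arm. The stated replacement rule does not correct it.

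The actual size is unknown. In the worst case, two removed non-improvers raise the nafamostat rate by 4.0 to 4.8 points and four raise it by 8.5 to 9.5 points, against a planned difference of 10 points. These figures assume no true effect, removal in one arm only and no improver among those removed. They would shrink if improvers or controls were also removed, and there is no shift if outcomes are still collected. One patient is 2.4 points (1/42), so even a few removals matter in a trial of this size.

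**What to change.** Reconcile the withdrawal and retention texts in {18b} with {20c} and {22}:

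1. Separate the end of study treatment from the end of trial follow-up.
2. Limit the end of follow-up to the patient's withdrawal of consent to follow-up, or closure of the trial or site.
3. State that patients with a serious adverse event, non-compliance or a stopped infusion are still followed for ordinal-scale status, vital status and adverse events through day 28 on the existing schedule.
4. Align the reporting sentence in {22} with this.

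The cost is a few sentences in an amendment, a notice to sites and a small amount of extra follow-up; ordinal-scale and adverse-reaction assessments are already scheduled to day 28. The change should reach sites while outcomes can still be collected. No change to the clinical rules for stopping the drug is proposed.

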### Data management {19}

#### Data forms and data entry

In this trial, all data will be entered electronically. This may be done at the participating site where the data originated. Original study forms will be entered and kept on file at the participating site. Participant files are to be stored in numerical order and stored in a secure and accessible place and manner. Participant files will be maintained in storage for a period of 3 years after the completion of the study.

#### Data transmission and editing

The data entry screens will resemble the paper forms approved by the committee. Modifications to data written to the database will be documented through either the data change system or an inquiry system. Data entered into the database will be retrievable for viewing through the data entry applications. The type of activity that an individual user may undertake is regulated by the privileges associated with his/her user identification code and password.

#### Data discrepancy inquiries

Additional errors will be detected by programs designed to detect missing data or specific errors in the data. These errors will be summarized along with detailed descriptions for each specific problem in data query reports, which will be sent to the data managers at the C&R research.

## Confidentiality {27}

All study-related information will be stored securely at the study site. All participant information will be stored in locked file cabinets in areas with limited access. All laboratory specimens, reports, data collection, process, and administrative forms will be identified by a coded ID [identification] number only to maintain participant confidentiality. All local databases will be secured with password-protected access systems. Participants’ study information will not be released outside of the study without the written permission of the participant.

## Plans for collection, laboratory evaluation, and storage of biological specimens for genetic or molecular analysis in this trial/future use {33}

To provide a resource for studies of inflammatory markers for COVID-19 pneumonia, white blood cell and plasma will be collected. Because the sample bank is a limited resource, proposals to use it will be evaluated in terms of scientific relevance, significance, and validity as well as the potential impact of the proposed study. The amount and type of material needed will also be considered, and the efficient use of material will be required. Strict confidentiality will be exercised and the information provided to investigators will not contain personal identifiers. Participation in this research is not required for continued participation in the nafamostat-mesylate trial. Although the original model consent form addresses genetic studies, participants will be asked to sign an additional consent form to document their consent to the collection and submission of additional blood samples for storage and future testing. The Global Clinical Central Lab (GCCL) in Yongin City, South Korea, will serve as the processing, aliquotting, and storage facility. Otherwise, the blood will be centrifuged in each institute and stored at sample bank. Plasma will be separated into aliquots and frozen.

## Statistical methods

### Statistical methods for primary and secondary outcomes {20a}

Intention-to-treat analysis and per protocol analysis will be conducted respectively, and intention-to-treat analysis will be performed as the main analysis.The categorical variable of the evaluation index will be analyzed using Pearson’s chi-square test, and the continuous variable will be analyzed using ANOVA or Kruskal–Wallis test.The virus removal rate on day 14, one of the secondary outcomes, will be analyzed using Pearson’s chi-square test.Time to clinical improvement will be assessed on all subjects by day 28. If there is no clinical improvement or a case of death by day 28, it will be recorded as day 28, and analyzed by Kaplan–Meier plot and log-rank test.

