## Eligibility criteria {10}

### Inclusion criteria

18 years old or olderPatients who have been confirmed of COVID-19 infection and has evidence for pneumonia
A.Confirmation of COVID-19 infection by RT-PCR of SARS-CoV-2B.Definite diagnosis of new infiltration of the lungs by chest CT scan of chest radiographic inspection3.Patients who are within 72 h of COVID-19 pneumonia confirmation4.Patients with 3 (hospitalization, not requiring supplemental oxygen) or higher in seven-category ordinal scale of clinical status5.Patients who are eligible for diagnosis/evaluation to chest CT scan and related to it6.Patients should be able to understand the essence of the clinical trial and to submit a written consent document. For the patients who can understand the nature of the research but cannot sign the document, a relative can agree to the study.

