### Sample size {14}

The sample size was calculated based on the assumption that superiority test (nafamostat treatment is right) of the treatment effect (effect size 10%) between two treatment groups (control group vs. nafamostat-treated group) will be carried out. The superiority margin is set to 0.05 (5%) based on the assumption that the nafamostat-treated group shows higher effect (90.0%) over the control group (80.0%). Nafamostat will be concluded as effective when the nafamostat-treated group shows 5% of higher effect compared to the treatment rate of the control group (80%). A one-sided significance level of 0.05 and power of 80% with equal allocation to two arms would require 42 patients in each arm of the trial.

Basic parameters for the sample size calculation are as follows:
Significance level, alpha = 0.05 (one-sided test)Power = 70%/80%/90%The ratio of the control group and the experimental group (nafamostat treatment) patients is 1:1Cure rate of the control group: 80%The cure rate of the experimental group (nafamostat treatment): 90%Superiority margin: 5%Expected drop out proportion: 5% (control, experimental each)

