## Assignment of interventions: allocation

### Sequence generation {16a}

Nafamostat mesylate with standard therapy group and standard therapy only group were assigned in a 1:1 ratio by block randomization method by institution.

The randomization generation program is as follow: randomization codes are generated using SAS® (SAS Institute, Cary, NC, USA) and assigned to a test group (nafamostat administration + standard treatment) or a control group (standard treatment) according to the generated assignment order.

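### As worded, the plan tests the seven-category clinical status without its order and leaves collected baseline values unused; both can be put right with no new data.

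*Protocol article*

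**What the plan says.** The section on statistical methods for primary and secondary outcomes {20a} assigns tests by type of variable. "The categorical variable of the evaluation index will be analyzed using" Pearson's chi-square; continuous variables go to ANOVA or Kruskal–Wallis; time to clinical improvement (TTCI) goes to a Kaplan–Meier plot and a log-rank test. No stratum or covariate is named.

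The other relevant statements are these:

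- **Sequence generation {16a}:** allocation is 1:1 "by block randomization method by institution". The study setting gives 10 hospitals.
- **Inclusion criteria:** patients enter at category 3 "or higher in seven-category ordinal scale of clinical status", so entry can range from no oxygen to ventilation or ECMO.
- **Primary outcome:** live discharge or a fall of two categories, so the baseline category is part of the definition.
- **Secondary outcomes:** these include the seven-category status at days 7, 14 and 28, change in NEWS from baseline to day 28, and change in log10 viral load.
- **Participant timeline {13}:** the ordinal scale, NEWS and RT-PCR are all recorded at screening.

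**The concern.** Pearson's test on a table of two arms by seven categories gives the same result however the columns are ordered. It spreads a one-directional treatment effect over up to six degrees of freedom, with few patients in several cells. A rank test or a proportional-odds model puts that effect into one degree of freedom.

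Baseline severity is likely to predict recovery, yet it is neither a randomisation stratum nor an analysis covariate. Changes in NEWS and viral load would be compared without adjustment for the starting value.

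With 84 patients, information discarded in this way cannot be spared. In an open-label trial, an adjustment chosen after the data are seen would carry little weight, so it has to be written down beforehand.

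**Working it through.** **1. The plan's own figure, as the reference.** Inputs from Sample size {14}: "Significance level, alpha = 0.05 (one-sided test"), control rate 80%, "The cure rate of the experimental group (nafamostat treatment): 90"%, and "A one-sided significance level of 0.05 and power of 80% with equal allocation to two arms would require 42 patients in each arm".

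- Simple difference: n = [z₀.₉₅√(2p̄q̄) + z₀.₈₀√(p₁q₁+p₂q₂)]²/δ² = (1.645×0.505 + 0.842×0.500)²/0.10² = 157 per arm before dropout.
- Superiority by the stated 5-point margin: (1.645+0.842)²×0.25/0.05² = 619 per arm, or 652 with 5% dropout.
- The stated 42 does not reproduce. Power of the unadjusted test at 42 per arm is Φ[(0.10√42 − 1.645×0.505)/0.500] = Φ(−0.365) = 36% one-sided, and 25% two-sided.

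The 36% is the baseline against which step 4 is read.

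**2. Ordinal status: Pearson against Wilcoxon.** The protocol gives no category distribution, so these control distributions over categories 1 to 7 are assumptions:

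- day 14: .15, .30, .30, .10, .06, .06, .03
- day 28: .50, .25, .10, .05, .03, .03, .04

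The treated arm is shifted by a common odds ratio (OR). Simulated power with 42 per arm, two-sided 0.05:

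| | Pearson | Wilcoxon |
|---|---|---|
| Day 14, OR 2 | about 18% | about 42% |
| Day 28, OR 2 | about 14% | about 36% |
| Day 14, OR 3 | about 46% | about 79% |
| Day 28, OR 3 | about 35% | about 69% |

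With no effect, Wilcoxon rejects in about 5% of runs. Pearson rejects in about 4% (day 14) and 3% (day 28), because the cells are sparse.

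**3. Does the gain survive other distributions?** Take OR = (0.9/0.1)/(0.8/0.2) = 2.25, N = 84, V = (N/12)(1 − Σp̄³), two-sided power = Φ(ln OR·√V − 1.96).

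| Control patients in categories 1 / 2 | V | Test using order | 6-df Pearson |
|---|---|---|---|
| 55% / 25% | 5.08 | 45% | 22% |
| 40% / 40% | 5.82 | 50% | 25% |
| nearly all improved in category 1 | 2.76 | 27% | 13% |
| nearly all improved in category 2 | 2.82 | 27% | 13% |

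The order-using test is ahead throughout, but by 14 points rather than 23–25 when patients pile up in one category.

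**4. Primary outcome, 80% vs 90%.** Simulation of 84 patients at 10 sites, blocks of four, assumed baseline mix 40/40/20% in categories 3, 4 and 5–6, one-sided 0.05. The columns give the assumed baseline effect on the log-odds per category. CMH is the Cochran–Mantel–Haenszel test.

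| Test | 0 | 1 | 1.5 |
|---|---|---|---|
| Pearson | 38% | 37% | 35% |
| CMH by baseline category | 36% | 38% | 39% |
| CMH by site | 37% | 37% | 34% |
| CMH by site × baseline | 30% | 30% | 30% |

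Across runs, stratifying by baseline category alone moves power by about −1 to +5 points, allowing for simulation error. Only with a very strong effect (2 per category) does it reach +7 to +8 (34% to 42%, and 38% to 45%). Site alone adds nothing. Crossing the two makes 10×3 = 30 strata of 84/30 = 2.8 patients, and many of them carry no comparison.

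**5. Baseline adjustment of scores.** The variance of a change score is proportional to 2(1−ρ), and under ANCOVA to 1−ρ². The ratio is (1+ρ)/2: 0.75 at ρ = 0.5 and 0.90 at ρ = 0.8. The reduction is therefore 25% or 10%, depending on a correlation that the protocol does not give.

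**6. Chance imbalance.** If 20% enter severe (an assumption), the SD of the between-arm difference in that share is √(0.2×0.8×2/42) = 0.087, about 9 points.

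**The case against.** The protocol never names a test for the ordinal status itself. Kruskal–Wallis, which uses order and with two arms is the Wilcoxon test, appears in the same paragraph, and the sponsor may have meant it. Strata and covariates are also often left to an analysis plan, which is not shown here. Both points stand in part: the loss of order is the likelier reading, not a stated fact. But the text does assign tests, and it restricts Kruskal–Wallis to continuous variables. If something else is meant, the wording needs correcting.

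It is also fair to say that the large contrasts belong to one secondary outcome and rest on assumed distributions and odds ratios. That stands, and step 3 shows the range.

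Three stronger readings are tempting, and the documents do not support them:

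- **That ignoring institution costs power.** With about eight patients per site, stratifying by site recovers none, and site × baseline strata lose 5 to 8 points in step 4. Institution belongs in an analysis only because the randomisation was blocked on it.
- **That the unadjusted tests are invalid or biased.** Randomisation protects them, and their error rate stays at or below about 5%. Uncorrected chance imbalance is a matter of precision.
- **That better tests would rescue the trial.** No variant of the primary analysis comes near 80% power at 84 patients.

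**Conclusion.** The point holds as an improvement that needs no extra data, mainly for secondary outcomes. On its natural reading the plan tests the seven-category status without its order, at about 14–18% power instead of 36–42% at an odds ratio of 2. The size of that gain depends on an unknown spread over the categories; its direction was the same in every case examined.

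Baseline category and baseline NEWS are collected and unused. For the primary outcome, using baseline category is worth only about −1 to +5 points on roughly 36%, unless it is very strongly prognostic. For NEWS the variance saving is about 10–25% for correlations of 0.8 down to 0.5. These results assume proportional odds, the stated baseline mix and, for the primary outcome, blocks of four. The sample size is a separate and larger problem.

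**What to change.** Amend the statistical methods section before the data are analysed:

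1. **Ordinal status at days 7, 14 and 28:** name a proportional-odds model with baseline category, or a Wilcoxon test stratified by it.
2. **Primary outcome:** Cochran–Mantel–Haenszel test stratified by baseline category (3, 4, 5–6) only. Say that the expected gain is small, and keep the unadjusted Pearson test as a sensitivity analysis.
3. **TTCI:** log-rank test stratified by the same baseline categories.
4. **NEWS and log10 viral load:** ANCOVA on the baseline value. For viral load, first confirm that the screening RT-PCR is quantitative, since the timeline does not say.
5. **Institution:** do not cross it with baseline category. Account for it only to match the randomisation, for example in a sensitivity analysis.

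The cost is a few sentences of statistical wording. The timeline already schedules the baseline assessments, and no patients, visits or endpoints change. Sample size {14} still has to be corrected separately.
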